### 3.2 Diagnostic Tests

Subjects will be asked to fast for at least 12 hours (nothing to eat or drink except water) prior to the screening (Visit 1) and end of study visit (Visit 6). At these visits, blood samples will be collected by venipuncture for analysis of CBC, AST, ALT, BUN, Creatinine, eGFR, glucose, electrolytes (Na, K, Cl) and lipid profile (total cholesterol, LDL-C, HDL-C and triglycerides. Additionally, blood samples (no requirement for fasting) will be collected by venipuncture for analysis of total RBC fatty acids at visits 2, 4, 5 and 6, and serum phospholipids at visits 2 and 3.

The volume of blood to be collected is approximately 14mL at visit 1, 10mL at Visits 2 and 3, 5mL at visits 4 and 5 and 19mL at visit 6. The total amount of blood collected over the 6 month study period will be approximately 63mL.

### 3.3 Allocation to Treatment

Each participant will be randomized in a 1:1 to ratio to either the investigational product (Ultimate Omega®) or comparator product Meg-3™ as follows:

| Study Arm       | Subject Number                 |
|-----------------|--------------------------------|
| Ultimate Omega® | N=30 (15 Males and 15 Females) |
| Meg-3™          | N=30 (15 Males and 15 Females) |
| Total    | 60                      |

### 3.4 Stopping Rules/Discontinuation

The investigator may withdraw any participant from this research if circumstances arise that warrant doing so. If a participant is withdrawn from the study for any reason, they will be asked to complete an early termination visit.

### **3.5 Concomitant Medication(s)**

#### **3.5.1 Permitted Medication(s)**

Prescription and OTC medications (including natural health products) not known to affect study endpoints are permitted if they have been consumed at a stable dose for the three months prior to Day 0.

Anti-hypertensive medications and thyroid hormone replacement therapy will be permitted provided subjects have been on a stable dosage (no change in dose) for the three months prior to screening (visit 1) and are not expecting to change dosage for the duration of the study.

Women of child-bearing potential will be permitted to continue using hormonal birth control.

#### **3.5.2 Prohibited Medication(s)**

Subjects will not be allowed to use the following medications during the study:

- Blood thinning agents (e.g. Warfarin)
- Corticosteroids
- Prescription anti-inflammatory medications
- Blood lipid-lowering medications or other lipid-binding medications (e.g. statins, fibrates, bile acid exchanger resin, phytosterols, niacin or its analogues, carnitine, supplements containing omega-3 fatty acids, polyglucosamines [Chitosan])
- Prescription or OTC medications (including NHPs) for weight loss or weight management

#### **3.5.3 Washout Period**

Subjects must not have used blood lipid-lowering medications or other lipid-binding medications, corticosteroids, anti-inflammatory medications or weight-loss programs or weight-loss medications in the 6 months prior to visit 1. Due to timing, it is unlikely that any subjects will be asked to wash out of the above medications or asked to stop diet programs in order to be eligible for this trial.

### **3.6 Measures to Minimize Bias**

The investigational products will be similar in size and shape and will be filled in similar primary packaging to minimize bias. All investigational product will have similar labels, differing only in the randomization number in order to blind the products.

## **4 SELECTION AND WITHDRAWAL OF SUBJECTS**

### **4.1 Number of Study Volunteers**

Sixty (60) participants will be enrolled in this study, with equal numbers of male and female subjects assigned to each group.

Subjects will be recruited for this study from the Guelph, Ontario region located in Southwestern Ontario, Canada. Advertisement of the study will include using NDI's electronic subject database to identify potential candidates, e-mail and online advertisement, and posted paper advertisements. Participants interested in the study will contact the study recruiters via phone, e-mail or online. Following this first contact, the study will be discussed in more detail and additional information not found on the recruitment material will be provided. Following this conversation, potential participants will schedule a first study visit appointment. During this appointment, further questions or concerns about the study will be addressed and subjects will read the informed consent. Subjects will be given the opportunity to take the informed consent home to consider participating in the study and respond to the recruiter, or alternatively, subjects may sign and agree to participate in the study immediately. Once the informed consent is obtained, subjects will be screened against the inclusion/exclusion criteria to determine whether they may participate in the study.

### **4.2 Inclusion Criteria**

An individual must meet all of the following inclusion criteria in order to be enrolled this study:

11. Male or female adults aged 18 – 35 (inclusive)
12. Healthy as determined from medical history
13. Non-smoker, or ex-smoker  $\geq 6$  months
14. Body mass index 18.5 – 24.9 kg/m^2
15. Female participants of childbearing potential (i.e. not surgically sterilized or post-menopausal greater than one year) must have negative urine pregnancy test and must be using an effective birth control method, defined as:
  - Continuous use of oral or long acting injected contraceptive for at least 2 months prior to study entry , or
  - Use of an intra-uterine device or implantable contraceptive, or
  - Use of double barrier methods of birth control, or
  - Abstinence from heterosexual intercourse
16. Willing to avoid alcohol consumption for 24 h prior to every clinic visit
17. Willing to maintain a stable body weight, activity level and dietary pattern except for use of the study products, as directed
18. Willing and able to provide informed written consent

### 4.3 Exclusion Criteria

A participant will be excluded from this study if any of the following criteria are met:

- E1. Individuals taking prescription or non-prescription health products that may affect the study endpoint (e.g. corticosteroids, prescription anti-inflammatory drugs, blood lipid-lowering drugs (e.g. statins, fibrates, bile acid exchanger resin, phytosterols, niacin or its analogues, carnitine, etc.) in the previous 6 months
- E2. Individuals taking any supplements with n-3 FAs, phytosterols, polyglucosamines (Chitosan) or other lipid-binding ingredients in the previous 6 months
- E3. Individuals who consume omega-3 fatty acid rich fish (salmon, mackerel, herring) more than twice per month
- E4. Unstable use (initiation or change in dose) of antihypertensive medications or thyroid hormone replacement medications within 3 months prior to visit 1
- E5. Use of any weight-loss programs or weight-loss medications (prescription or over-the counter) including, but not limited to, lipase inhibitors, within 6 months prior to visit 1 and throughout the study
- E6. Pregnancy or lactation, or participant unwilling to take appropriate contraceptives for the duration of the study
- E7. History of blood clotting disorders or use of coagulation-inhibiting drugs (e.g. warfarin)
- E8. Presence of major diseases such as diabetes, gastrointestinal, endocrine, cardiovascular, renal, or liver disease
- E9. History of neurological disease (e.g. Parkinson's disease, stroke, traumatic brain injury, etc.)
- E10. History of cancer (excluding non-melanoma skin cancer and basal cell carcinoma) in past 5 years
- E11. Uncontrolled hypertension defined as a seated resting systolic blood pressure  $\geq 140$  mmHg and/or diastolic blood pressure  $\geq 90$  mmHg
- E12. Abnormal laboratory test results of clinical significance, including, but not limited to, ALT or AST  $\geq 1.5X$  the upper limit of normal at screening (visit 1)
- E13. TG  $\geq 400$  mg/dL ( $\geq 4.52$  mmol/L) at screening (visit 1)
- E14. Presence or history (past 6 months) of alcohol or drug abuse; alcohol use of  $>2$  standard alcoholic drinks per day
- E15. Participant has a known allergy or intolerance to fish/fish oil or any of the ingredients in the test products
- E16. Participant is vegan
- E17. Participant is unwilling or unable to abide by the requirements of the protocol
- E18. Any condition that would interfere with the participant's ability to comply with study instructions, might confound the interpretation of the study, or put the participant at risk
- E19. Participant has taken an investigational medicine or has participated in a research study within 30 days prior to the first study visit

#### 4.4 Withdrawal Criteria

A participant may end his/her participation in a study at any time without consequence. If a participant withdraws from the study, the Investigator will make a reasonable effort to determine the reason for withdrawal from the study and record any adverse events experienced by the subject.

**Personal reasons (participant initiated):** As stated in the ICF, participants will be informed that their participation in the study is optional, and they can withdraw from the study at any time, without consequence or prejudice.

**Clinical judgment of investigator/physician:** A participant could also be withdrawn from the study if, in the opinion of the treating physician, it is not in the participant's best interest to continue (e.g. pregnancy, adverse events, need for prohibited medication, illness). In the event that a female participant becomes pregnant during the study, she will be withdrawn from the study immediately, and the pregnancy followed to resolution. Further, spontaneous abortion or any congenital anomaly/birth defect, in the case of a live birth, must be reported as an SAE to the REB and Health Canada within 15 days of becoming aware of the event. All serious adverse events will result in withdrawal from the trial.

**Protocol violation:** Participants who fail to comply with the protocol may be removed at the discretion of the investigator.

Subjects Participants who wish to withdraw from the study will be asked for their reason(s). Reason(s) for participant withdrawal will be recorded on the CRF for all participants who sign the informed consent form.

Reasons for withdrawal will be documented as one of the following:

- W.1 Participant requests withdrawal from the study
- W.2 Participant withdraws consent
- W.3 AE makes the continuation of the participant impossible or inadvisable
- W.4 Participant was incorrectly included in the study (discovered after enrollment not to have met the protocol entrance criteria)
- W.5 Participant refuses to comply with required study procedures
- W.6 Participant has confirmed pregnancy

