### **3.1.7 Early Termination/Discontinuation Visit**

Participants may withdraw voluntarily from participation in the study at any time. Subjects will be encouraged to visit the clinic for an early termination visit. At this visit, subjects will be encouraged to return study product and diaries, have blood pressure, heart rate and weight measured and provide a blood sample for analysis of safety parameters (hematology and clinical chemistry).

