#### **7.1.7 Follow-up of AEs**

AEs, especially those for which the relationship to investigational product is suspected, should be followed up until they have returned to baseline status or stabilized.

If after follow-up, return to baseline status or stabilization cannot be established an explanation should be recorded in the study record.

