## **8.3 Analytical Populations**

### **8.3.1 Intent-To-Treat Population**

Any subject known to start treatment (known to have taken  $\geq 1$  dose of study product) and completing at least one post-baseline visit will be included in the analysis of efficacy (intention-to-treat population).

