## **8.4 Statistical Methods**

An effectiveness analysis based on the intent-to-treat population will be performed for all efficacy outcomes. Continuous variables will be presented as means with standard errors of the mean (SEM). Categorical variables will be shown as frequencies or proportions. Numerical efficacy endpoints will be

formally tested for significance by analysis of covariance. The dependent variable will be the post-baseline value; the factor of interest will be the treatment group (product) and value at baseline (usually visit 2, except for some laboratory tests [e.g. lipid profile] where baseline is visit 1) will be the covariate.

The ANCOVA approach differs from the simpler approach of comparing changes from baseline between products in that the ANCOVA adjusts for baseline in a more sophisticated way than simply subtracting it from the end of study value. The adjustment allows the ANCOVA to compensate for regression to the mean, floor effects, and other ways that the baseline value could influence change from baseline.

Where values being summarized as significantly non-normally distributed, as assessed by the Anderson-Darling test, a non-parametric test, such as the Wilcoxon or Mann-Whitney U test will be used.

A within-group analysis, if warranted, may be performed using a Student's paired samples t-test or Wilcoxon sign rank test.

All calculations and analyses will be performed using SAS version 9.2 or higher. For all statistical inferences, the tests will be performed at the two-sided, 0.05 level of significance.

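### Withdrawal rules take randomised participants out of the trial, not only off product, and the exit visit takes no fatty acid sample, so obtainable primary endpoint data are lost in an analysis called intention-to-treat

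*Protocol*

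**What the plan says.** Section 4.4 (Withdrawal Criteria) makes leaving the trial automatic after any serious adverse event (SAE), whether related or not: "All serious adverse events will result in withdrawal from the trial". On non-compliance it says: "Participants who fail to comply with the protocol may be removed at the discretion of the investigator". It gives no threshold. The section headed Stopping Rules/Discontinuation adds a general power for the investigator to withdraw participants, and describes what follows: "If a participant is withdrawn from the study for any reason, they will be asked to complete an early termination visit".

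At that visit (3.1.7) participants are encouraged to return product and diaries, to have blood pressure, heart rate and weight measured, and to "provide a blood sample for analysis of safety parameters (hematology and clinical chemistry"). Fatty acids are not listed.

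The primary endpoints (6.1) are RBC EPA and DHA at 24 weeks and serum phospholipid fatty acids at 1 month. Under Diagnostic Tests, RBC fatty acids are sampled at Visits 2, 4, 5 and 6, and serum phospholipids at Visits 2 and 3.

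For the analysis, a participant who has taken at least one dose and is "completing at least one post-baseline visit will be included in the analysis of efficacy (intention-to-treat population"). Section 8.4 continues: "An effectiveness analysis based on the intent-to-treat population will be performed for all efficacy outcomes". Section 8.6 fills missing primary and secondary endpoint values by last observation carried forward (LOCF).

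**The concern.** Each rule is unremarkable alone. Together they turn a decision about product into a loss of endpoint data. A participant who has an SAE, or is judged non-compliant, may be willing to give a blood sample at the remaining visits. The protocol ends those visits and takes no fatty acid sample on the way out.

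The consequence is sharpest for the RBC endpoint, because there is no RBC sample at Visit 3. A participant who attends Visit 3 and is removed before Visit 4 belongs to the efficacy population, but the only RBC value on file is from Day 0. Carried to week 24, it records no response after a month or more of supplementation.

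The stake is a small contrast measured in 60 people. Losing observed week-24 values for reasons that arise after randomisation weakens the comparison. It would distort the comparison if one product led to more removals than the other. A statistical analysis plan cannot repair this later, because the samples will not have been drawn.

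**Working it through.** **Planned loss.** Section 8.2 expects 24 completers per group and 20% attrition. 24 / (1 − 0.20) = 30 per group, which reproduces the plan's figure. Expected loss is 0.20 × 30 = 6 per arm, or 12 of 60. No power, effect size or SD is stated, so there is no power figure to check.

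**What happens to the RBC endpoint, by time of removal** (taking the required post-baseline visit to be a scheduled one)
- Before Visit 3: outside the efficacy population.
- Between Visit 3 (Day 28) and Visit 4 (Day 84): in the population, with the Day 0 value carried to week 24.
- Between Visit 4 and Visit 6: in the population, with the Visit 4 or Visit 5 value carried to week 24.

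**Labelled dose contrast** (5.2 Description of IP and 5.1 Description of Comparator Product)
- Investigational product: 5 × (325 + 225) = 2750 mg/day EPA + DHA.
- Comparator: 5 × (300 + 200) = 2500 mg/day.
- Ratio: 2750 / 2500 = 1.10.

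Assumption: the RBC rise is proportional to labelled dose. Set the comparator rise to 1.00 and the investigational rise to 1.10, so the true difference is 0.10. With k1 and k2 participants of 30 scored at Day 0 in the investigational and comparator arms, the expected difference is

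(30 − k1)/30 × 1.10 − (30 − k2)/30 × 1.00.

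| k1 | k2 | Difference | Share of true |
|---|---|---|---|
| 0 | 0 | 0.100 | 1.00 |
| 6 | 6 | 0.080 | 0.80 |
| 1 | 0 | 0.063 | 0.63 |
| 3 | 0 | −0.010 | −0.10 |
| 0 | 3 | 0.200 | 2.00 |

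Each such participant lowers that arm's mean response by 1/30 = 3.3% of its value. The 6-and-6 row is an upper case, in which all planned attrition occurs in this window.

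**How likely an imbalance of 3 is.** The window from Visit 3 to Visit 4 is 84 − 28 = 56 of 168 days. If losses are uniform in time (assumption), it holds 56/168 × 20% = 6.7% per arm. The protocol does not say what share of attrition is investigator-driven, so I show a range. With independent Binomial(30, p) counts in the two arms, P(|k1 − k2| ≥ 3) is:
- p = 6.7% (every loss in the window): 0.187, about 19%.
- p = 3.3% (half of those investigator-driven, assumption): 0.070, about 7%.
- p = 2% (assumption): 0.026, about 3%.

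These are chance imbalances under the same removal rate in both arms. They do not measure bias.

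**The SAE route.** No SAE rate is given. At assumed rates of 1%, 2% and 5%, 0.6, 1.2 and 3.0 of the 60 participants would leave for this reason. In healthy adults aged 18 to 35 the lower end is the more plausible.

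**The case against.** The strongest reply is that section 8.3.1 excludes nobody for withdrawal, an SAE, non-compliance or ineligibility. Anyone with one dose and one post-baseline visit stays in, and 8.6 says how gaps are filled. That is right: for these participants it is observed values that are lost, not the people. It does not help the endpoint, since the filled value can be the Day 0 one.

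It is also fair that SAEs should be few, that removal for non-compliance is permitted and not required, and that no document says how often it would be used. Some who refuse procedures would not return for sampling anyway.

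Four stronger readings are tempting, and the protocol does not support them.
- A reader might apply the imbalance calculation to the whole 20% attrition, which gives about 42%. That figure includes withdrawn consent, which no rule change recovers, and losses outside the window in which the Day 0 value is carried.
- A reader might infer bias between products. The products are similar in size and shape, both are lemon-flavoured, and the trial is double-blind. Nothing in the protocol suggests different tolerability. Equal losses attenuate the contrast.
- A reader might see a contradiction with 7.1.7, under which adverse events "should be followed up until they have returned to baseline status or stabilized". That is safety follow-up and is compatible with having left the trial. Section 4.4 itself combines withdrawal for pregnancy with follow-up of the pregnancy.
- A reader might take W.4 and W.5 as removal rules. They are codes for recording a reason.

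**Conclusion.** The point holds as a defect of trial conduct. The protocol ends endpoint sampling for participants who may still consent to it, takes no fatty acid sample when they leave, and scores some of them as having no RBC response in an analysis labelled intention-to-treat.

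Its size is modest and uncertain. Equal losses would leave at worst 0.80 of the true difference, if all planned attrition were scored at Day 0. A single unmatched case in the investigational arm would reduce a 10% contrast to 6.3%, assuming response proportional to labelled dose. An imbalance of three or more in the critical window has a probability of about 3% to 19%, for assumed removal of 2% to 6.7% per arm. Bias would need removal rates that differ by product, and the protocol gives no evidence of that. The case rests mainly on the discretionary non-compliance route, whose frequency is unknown.

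**What to change.** In Stopping Rules/Discontinuation and in 4.4, distinguish discontinuing product from withdrawing from the study. Where consent remains and the investigator sees no safety objection, participants who stop product or are judged non-compliant keep the fatty acid samplings already scheduled and are analysed as randomised. For those who do leave, add the fatty acid sample to the early termination visit in 3.1.7. Reconcile 3.1.7, Stopping Rules/Discontinuation, 4.4, 8.3.1 and 8.6 on what happens to endpoint data after product stops. When product is stopped remains a clinical decision and is not addressed here.

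The cost is protocol wording, plus visits and assays for a few participants who would otherwise have left. The visits are already planned for 30 per arm. The only added procedure is one fatty acid sample at early termination. The sample size does not change.

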## **5 INVESTIGATIONAL PRODUCT**

### **5.1 Treatment Groups**

The study will consist of two treatment groups. Participants will be randomly assigned, in equal proportions, to the two treatment groups. An equal number of male and female subjects will be randomized to each group. Alpha-numerical codes will be used to identify participants. At randomization each subject will receive a unique numerical randomization code.

### **5.2 Description of IP**

The investigational product (IP) is Ultimate Omega® [NPN 80003338]

Manufacturer: Nordic Naturals Inc.

Formulation of the IP (per capsule):

Medicinal Ingredients: Fish Oil 1000mg (providing 325mg EPA, 225mg DHA and 90mg other Omega-3 Fatty Acids)

Non-medicinal ingredients: Gelatin, Glycerin, Natural Lemon Flavour, Rosemary extract, Water

### **5.1 Description of Comparator Product**

The comparator product is Meg-3™ Formulation of the comparator product (per capsule):

Medicinal Ingredients: Fish Oil 1000mg (providing 300mg EPA and 200mg DHA)

Non-medicinal ingredients: Gelatin, Purified Water, Natural Lemon Flavour, Rosemary extract and Vitamin E

## 5.2 Investigational Product Packaging and Labeling

The IP and comparator products will be provided by the sponsor. Study products will be packaged in white HDPE bottles with a count of 150 capsules per bottle. The study products will be labeled with compliant labels. An example of a compliant label in Canada for a natural health product is provided below:

|                                                                                                                                                                                                                                                                                                           |                                           |
|-----------------------------------------------------------------------------------------------------------------------------------------------------------------------------------------------------------------------------------------------------------------------------------------------------------|-------------------------------------------|
| Protocol No. (No. de Protocole): 1007-008-PRO-040414 Randomization No. (No. de Randomisation): <insert>                                                                                                                                                                                                   |                                           |
| Product name and lot number (Nom du Produit et No. de Lot):
Ultimate Omega® [NPN 80003338] Lot 141179 or Meg-3™ Lot 153143                                                                                                                                                                             |                                           |
| Contains: 150 Capsules                                                                                                                                                                                                                                                                                    | Expiry date (Date d'expiration): Jun 2017 |
| Investigational Natural Health Product (Produit de santé naturel expérimentale)
Use under the supervision of a qualified investigator
(Pour être utilisé sous la supervision d'un chercheur qualifié).                                                                                              |                                           |
| Sponsor (Promoteur) / Manufacturer (Promoteur & Fabricant):
Nordic Naturals
[name]
[name]                                                                                                                                                                             |                                           |
| For investigational use only (Utilisation investigational seulement). Keep out of reach of children (Tenir hors de portée des enfants). Store at room temperature (Conserver à température ambiante).
If any problems or questions (Si des problèmes ou des questions), [contact]. |                                           |
| Investigator Name: [name]                                                                                                                                                                                                                                                                       | [contact]                       |
| Subject No.: _____                                                                                                                                                                                                                                                                                        | Subject Initials: _____                   |
| Date dispensed: _____                                                                                                                                                                                                                                                                                     | Date returned: _____                      |

